#### Messaging

MI-BP provides users with 4 different types of messages, which are sent via push notification and in-app messaging. These messages include educational messaging, motivational messaging, tailored messaging, and daily medication reminders. In addition to the daily medication reminders, MI-BP sends about 7 messages per week. To enhance long-term engagement with the intervention from participants, message content, frequency, and timing are varied and tailored wherever possible, to maximize user engagement (see Multimedia Appendix 1 for sample messages and Figure 1 for screenshots of the MI-BP app).

##### Educational Messaging

MI-BP provides users with educational messaging via push notification and in-app messages. Educational messaging topics include tips pertaining to tracking BP, physical activity, and sodium; tips pertaining to increasing physical activity, improving diet, increasing medication adherence, lowering BP, and making or maintaining behavior changes; and tips pertaining to overcoming barriers to behavior changes.

##### Motivational Messaging

In addition to educational messaging, motivational messaging and words of encouragement to meet goals are also provided to MI-BP users.

##### Tailored Messaging Relevant to Individual Participants

MI-BP also provides tailored messaging to users, including tips for overcoming specific, self-reported barriers to behavior changes (assessed at baseline and repeated at 6 months) and previous history of app usage (eg, reminders to sync or log data), along with reminders about self-monitoring protocols, and support for goal attainment, where applicable. For example, positive reinforcement messages are sent to the participants when goals are met, and action-oriented messages promoting behavior changes are sent when goals are not met.

##### Medication Reminders

MI-BP also enables users to set up daily medication adherence reminders (see Figure 1 for screenshots of the MI-BP app). The number of messages and the timing of those messages are customizable by the user to account for multiple antihypertensive medications and multiple doses per day. Although the study staff help users set up reminders at the time of randomization, users are free to modify these reminders at any time.

### Clinical Setting

Participant recruitment occurs at the Detroit Medical Center (DMC) in the EDs of Detroit Receiving Hospital (DRH) and Sinai-Grace Hospital (SGH), both located in Detroit, Michigan. In Detroit, where 59% of the population lives in a medically underserved area, and an equal number (32.5% of individuals and 27% of families) live in poverty [25], reliance on the ED for primary care of chronic conditions such as HTN is commonplace. Once enrolled, the study participants complete all subsequent visits on the campus of WSU, in the Clinical Research Service Center (CRSC).

#### Recruitment

Recruitment occurs on site in the 2 EDs with active screening 24 hours per day, 7 days per week, 365 days per year. All patients that enter the ED are screened by trained research staff through the DMC electronic medical records system (Citrix Systems, Inc). Once a patient is deemed eligible, a research staff member approaches the patient’s treating physician and asks if this study will benefit the patient’s medical needs. Upon agreeance of the physician, the patient is then approached and educated on the study. If the patient is interested and agrees to participate in the study, an informed consent form is signed by the patient before any study procedure is done. Participants recruited to the MI-BP study are also approached during their baseline appointment to participate in an optional biorepository of blood samples collected during the trial. The biorepository has a separate consent process, which states that the participants’ data from MI-BP are associated with their blood sample.

### Eligibility Criteria

#### Inclusion Criteria

To be enrolled, potential participants must be African American and between the ages of 25 to 70 years, have been previously diagnosed with HTN, have a smartphone compatible with the mobile intervention, and have uncontrolled BP (SBP>135 mmHg) at triage and on repeat measurement using the BpTRU (Smiths Medical PM Inc, Waukesha, WI) device at least 1-hour post triage vitals.

#### Exclusion Criteria

Individuals who are pregnant; have serious existing medical conditions that may make BP control difficult or necessitate frequent hospitalization (ie, previous diagnosis of resistant HTN, steroid-dependent asthma or emphysema, cirrhosis or hepatic failure, stage C or D chronic heart failure, stage IV or V chronic kidney disease, and terminal cancer or ongoing active chemotherapeutic or radiation therapy); have a history of other serious medical conditions (eg, stroke, dementia, myocardial infarction or known coronary artery disease); or have a history of alcohol or drug abuse as determined by the CAGE-AID-Cut down, Annoyed, Guilty, Eye-opener Adapted to Include Drugs questionnaire (excluded if 2 or more) [26] are excluded.

Those who meet the eligibility criteria are enrolled in the ED and given a subsequent appointment for follow-up 1 to 2 weeks later at the WSU CRSC where BP is remeasured using the BpTRU device. To ensure that we are indeed including a sample with uncontrolled HTN, the participants who have a SBP<130 mmHg at that time are deemed ineligible and excluded from the study.

### Sample Size

On the basis of data from our previous studies, we estimate that 30% of usual-care participants will achieve BP control (BP<130/80 mmHg) by 1 year. We consider at least 17.5% higher control rates for the intervention arm to be clinically meaningful. On the basis of a 2-sided chi-square test of comparing 2 proportions at a 5% level of significance, the power for detecting the difference between MI-BP self-monitoring arm and usual care is 90%, with 161 participants per arm. Allowing for 19% attrition based on our previous work in similar patient populations, we plan to recruit 198 participants per arm, for a total of 396 participants. It is anticipated that at the end of trial, both groups will improve on average SBP. We estimate a 10- and 17- point drop in the usual care and MI-BP arms, respectively, at 1 year. Further, a constant between-subject SD of 10 mmHg is assumed, along with an intra-subject correlation of 0.5. With 161 subjects per arm, we can detect a group-by-time interaction with power >95% at 5% level of significance.

### Procedures

Once enrolled and consented in the ED (weeks −1 to −2), participants are scheduled for a return visit in 1 to 2 weeks for their baseline appointment (week 0) at the WSU CRSC. As noted above, only those individuals with persistent uncontrolled HTN at this visit are eligible to remain in the study. Baseline data collection also occurs at week 0, and participants are given a prescription for antihypertensive therapy, and referrals to primary care are made by study physicians. For the participants already taking antihypertensive medications and who have an existing relationship with a primary care provider (PCP), we contact their PCP to inform them of our algorithm-based approach to antihypertensive therapy and work to coordinate any medication adjustments. In week 2, participants undergo medication titration, the process of adjusting antihypertensive medication dosages to ensure appropriate and optimal treatment, and are then randomized into 1 of the 2 study arms. Please see Multimedia Appendix 2 for the medication algorithm used in this trial for titration. From our previous unpublished work, we have determined that attrition is greatest between ED recruitment and the first follow-up visit. Thus, by delaying randomization until after this run-in period, we anticipate fewer participants will be lost to follow-up. Moreover, to reduce attrition, at baseline, we collect contact information for up to 3 alternate contacts, who we may call if we are unable to locate the participant to schedule data collection visits. Our staff also heavily rely on telephone calls and text messaging to participant smartphones to communicate as needed to coordinate scheduling, which tend to be the preferred modes of communication among participants. If needed and requested by participants, we also provide transportation to data collection visits. The MI-BP study staff take a participant-centered approach to trial management and are available daily to meet participant needs. Participants are encouraged to call the staff for any questions pertaining to their medications, their BP, technical issues with the intervention, or other issues that arise (see Figure 2 for a flow diagram of trial procedures). Peer-review report from the Center for Scientific Review has been provided in Multimedia Appendix 3.

Randomization is stratified by sex in blocks of equal size, allowing us to investigate sex as an effect-modifying biological variable. To control response fatigue, we created 6 different permutations of the baseline survey, each with a different order of instruments, which are also balanced within blocks. The research assistants responsible for arm allocation are blinded to block size to prevent contamination.

After randomization, all study materials, including any equipment and/or materials, are distributed to the participants according to the treatment arm. Medication titration occurs again at week 8, and at subsequent follow-up visits at weeks 13, 26, 39, and 52 to ensure optimal treatment. Data collection follow-up visits take place at weeks 13, 26, 39, and 52, where a consistent set of study measures is collected—BP, health status, weight, adherence to BP measurements, physical activity, sodium intake, and medication adherence self-monitoring. Technology acceptance measures, including perceived ease of use and perceived usefulness, are also collected.

For medication titration and follow-up visits, patients are instructed to bring their HTN medications with them so pill counts can be conducted. Pill counts are used to avoid prescribing potentially harmful up-titration in antihypertensive therapy for patients with elevated BP at follow-up visits that may be because of medication noncompliance. For patients who self-report not filling prescriptions between visits, or when the expected number of pills found in the participant’s medication bottles (based on dosage and dispense date) suggests a less than 80% medication adherence, we continue with the same regimen without adjustment. We also monitor for any potentially harmful renal or metabolic issues at weeks 0, 26, and 52 and adjust medications accordingly. In addition to the medications, participants are instructed to bring study-dispensed devices so data can be downloaded, and adherence to self-monitoring behaviors can be ascertained.

Finally, to measure sodium intake, at weeks 0, 26, and 52, participants are given supplies to collect 24-hour urine for sodium measurement. This test reveals the amount of sodium ingested in the previous 24 hours and may identify whether sodium intake has been reduced. Study staff collect these specimens directly from the participants at their home to ensure compliance. All medication titration and study follow-up visits are free; however, participants are responsible for the cost of medications, PCP visits, or copays, as applicable.

All the participants are encouraged to contact the study staff for any assistance needed for the study, including assistance for technical and nontechnical matters. This is accomplished through in-app messaging (intervention arm only), as well as through handouts given at randomization and in person at each data collection visit.

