#### Blood Pressure

We are collecting 2 types of BP data in this trial: in-clinic and home BPs. In-clinic BPs are assessed for every patient, regardless of trial arm, at every study visit by a trained study staff member using a BpTRU BP monitoring device. Home BP data are also collected from the intervention-group participants as a part of their use of the MI-BP app.

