### Statistical Analysis Plan

#### Analysis of Blood Pressure Control

To determine the effect of MI-BP on BP at 1 year (aim 1) and to determine whether BP control is better in intervention-group participants compared with controls (hypotheses 1a), we will conduct a comparative analysis using a logistic regression with BP control as the outcome and study arm as the primary factor, controlling for demographic characteristics such as age, gender, medical history, baseline levels of functional status, health literacy, HTN knowledge, self-efficacy, and baseline BP at randomization. To determine whether mean SBP is better in the intervention group, compared with controls (hypothesis 1b), differential reduction in the coprimary outcome of SBP will be assessed in a linear mixed-effects regression framework, with time (baseline and end-of-trial), group, and time-by-group interaction as the primary independent variables. The subject-level characteristics used in the analysis of the primary outcome will be controlled in the regression model.

To determine the effect of MI-BP on secondary outcomes (aim 2), we will also use linear mixed-effects regression models with the secondary outcomes of interest as the dependent variables and week (as a continuous variable), study group, and week-by-group interaction as the primary independent variables. All appropriate model diagnostics will be carried out.

During data analysis, we will statistically address missing data resulting from incomplete data collection or participant attrition using the multiple imputation technique. Missing values will be imputed by repeatedly and iteratively fitting a sequence of regression models; it is a technique that is flexible in allowing different types of variables (categorical and continuous) to be imputed together without requiring any multivariate joint distributional assumption. Missing values are sequentially updated using bootstrap or Markov Chain Monte Carlo based on multiple regression models with other variables as covariates. This procedure will be conducted for 10 repetitions or cycles, a number considered adequate for most applications, thereby constructing an *imputed* dataset. Results from the 10 regressions will be combined with the imputed data using Rubin’s formula [39].

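### Baseline blood pressure is not tied to one visit: baseline is week 0, randomization is week 2, and the two coprimary analyses describe their starting reading differently

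*Protocol article*

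**What the plan says.** **Timeline (Procedures; Exclusion Criteria).** Week 0 is the baseline visit: "Baseline data collection also occurs at week 0, and participants are given a prescription for antihypertensive therapy". The check on uncontrolled BP is made at that visit too: "the participants who have a SBP<130 mmHg at that time are deemed ineligible and excluded from the study". Two weeks later, "In week 2, participants undergo medication titration, the process of adjusting antihypertensive medication dosages to ensure appropriate and optimal treatment, and are then randomized". No BP condition is stated at week 2. The delay is deliberate: "by delaying randomization until after this run-in period, we anticipate fewer participants will be lost to follow-up".

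**Analysis (Analysis of Blood Pressure Control).** The covariates of the logistic model for BP control end with "and baseline BP at randomization". The mixed model for SBP is specified "with time (baseline and end-of-trial), group, and time-by-group interaction as the primary independent variables", with no visit named. The article adds that the SBP model will control for the same subject-level characteristics as the control model.

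**Available readings (Blood Pressure; Table 1).** "In-clinic BPs are assessed for every patient, regardless of trial arm, at every study visit", and Table 1 lists week 2 as a visit in both arms. A week-2 clinic reading should therefore exist for everyone.

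**Planning figures (Sample Size).** Falls of 10 and 17 points are assumed at 1 year, with SD 10 mmHg and intra-subject correlation 0.5. The visit from which the falls are counted is not given.

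**The concern.** On the article's own timeline, baseline and randomization are two visits a fortnight apart, with a study prescription issued at the first and titration at the second. A phrase that joins the two therefore identifies no single reading. An analyst could take week 0 for one coprimary model and week 2 for the other and claim to have followed the text both times.

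Three things depend on the choice:

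- **Within-arm falls.** Counted from week 0, they include whatever the run-in prescription achieved before allocation, plus regression to the mean from a reading selected to be at least 130.
- **Population.** The stated purpose of the check ("To ensure that we are indeed including a sample with uncontrolled HTN, the participants who have a SBP<130 mmHg at that time" are excluded) is met at week 0 only. Some participants may already be below the control limit when randomized, and a week-0 baseline cannot show who they are.
- **Precision.** Two pre-allocation readings are available. A plan that uses only one, or only a change score, gives up information already collected.

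**Working it through.** **1. The plan's own figures.**
- Control, 30% v 47.5%, two-sided 5%, 90% power: n = 161 per arm without continuity correction (power at 161 = 90.0%).
- Attrition: 161/0.81 = 198.8, against 198 stated; the gap is immaterial.
- SBP: SD of change = 10 × √(2(1 − 0.5)) = 10. A 7 mmHg difference with 161 per arm has power 99.999%, so the stated >95% holds.
- For baseline-to-week-52 correlations from 0.1 to 0.7, change-score power stays above 99.6%. The SD of change would have to reach about 17.4 mmHg for power to fall to 95%.

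The choice of baseline therefore does not alter the sample size.

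**2. Is the between-arm contrast affected?** Simulation with SD 10, correlation 0.5 between all visits, selection at week 0 of SBP ≥130, and a true effect of 7 mmHg. Assumed, not in the article: mean SBP before selection of 140, 145 or 150, and a common run-in drop of 0, 5 or 10 mmHg. The between-arm difference in change is about −7.0 from week 0 and about −7.0 from week 2 in every scenario. There is no bias.

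**3. Within-arm falls.** In the same simulation the selected week-0 mean overstates the underlying level, so regression to the mean adds 0.3 to 1.4 mmHg to the usual-care fall. Example with mean 140 and a 5 mmHg run-in drop: usual care falls 11.4 mmHg from week 0 but 5.0 mmHg from week 2.

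**4. Share with SBP<130 at randomization.**

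| Run-in drop (assumed) | Share below 130 |
|---|---|
| 0 mmHg | 2–11% |
| 5 mmHg | 6–25% |
| 10 mmHg | 15–44% |

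The ranges cover the three assumed means. This is SBP alone. Control is defined as <130/80, so the share already controlled would be no larger.

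**5. Precision under the plan's SD 10 and correlation 0.5.** Let v be the variance of the week-0 reading after truncation at 130: 63.0, 77.3 and 88.6 for means 140, 145 and 150.
- Change from week 0: variance = 75 + 0.25v = 90.7 to 97.2.
- Change from week 2: variance = 100, which is 3–10% **higher**.
- Week 52 adjusted for week 0: 100 × (1 − 0.5²) = 75.
- Week 52 adjusted for week 2 only: 72.5 to 74.3, which is 1–3% lower than 75.
- Week 52 adjusted for both: R² = 2 × 0.5²/(1 + 0.5) = 1/3, so 66.7. Against week 0 alone, 66.7/75 = 0.889, or 11% lower.

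**6. Precision if the early drug response varies between people.** Assumed: stable level N(143, 8), reading error SD 7, early-response SD 2 to 8, later change SD 5, and the same selection. Adjusting for both readings cuts the adjusted variance by 12% (SD 2) to 36% (SD 8) relative to week 0 alone. None of these SDs is in the article, and they give a week-52 SD of 11.4 to 13.8 rather than 10.

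**The case against.** The strongest reply is that the analysis section, read literally, already does the right thing. BP at randomization means week 2, and the SBP model inherits the control model's covariates, so both models adjust for week 2. That reading is possible, and it rules out saying that the plan definitely starts the SBP comparison at week 0. It does not remove the conflict, because the SBP model's first time point is still just baseline, which Procedures places at week 0.

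A reader might go further and infer that the SBP comparison is biased, or that the trial is mis-sized. The documents do not support this. Both readings precede allocation and the run-in is common to both arms, so its effects cancel. Nor is week 0 an untreated reading: Procedures provides for participants already on antihypertensives.

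It is also tempting to claim a large gain from simply moving baseline to week 2. Under the plan's own SD and correlation that swap makes a change score slightly worse and barely helps an adjusted analysis. Larger gains from the swap need a between-person spread in early response that the article does not give.

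Three further replies stand. The run-in has a stated reason, attrition. The uncontrolled check is promised only for week 0, so its absence at week 2 breaks no stated rule. And the stated aim includes maintaining control, so entering with BP already below the limit is not contradictory. Finally, an article may leave visit definitions to a fuller plan, but here the article itself uses two labels that its own timeline separates.

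**Conclusion.** The concern holds as an internal conflict over which reading is baseline for the coprimary analyses, with modest consequences. The between-arm estimate, the 161/198/396 figures and the SBP power are unaffected.

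The cost lies elsewhere. The 10- and 17-point falls have no stated origin; from week 0 they would include the whole run-in response plus about 0.3–1.4 mmHg of regression to the mean. An unknown share of participants enters already below SBP 130. About 11% of adjusted variance is forgone if week 0 alone is used where both readings could be.

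The 11% rests only on the plan's SD of 10 and a correlation of 0.5 taken to apply between all visits. The regression-to-the-mean figures also need the assumed pre-selection means, and the shares below 130 need both those means and the assumed run-in drops. They show a plausible range and are not estimates.

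**What to change.** Reconcile Procedures with Analysis of Blood Pressure Control:

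1. Define baseline BP at randomization, for both coprimary analyses, as the week-2 clinic BpTRU reading taken before allocation, and state that order within the visit.
2. Add the week-0 reading as a further covariate in both models, rather than relying on a change score from week 2 alone. For SBP, the simplest form is week-52 SBP regressed on arm with both readings as covariates. In a two-time-point mixed model with complete data, a covariate entered only as a time-constant main effect leaves the time-by-group estimate equal to the difference in mean change. The gain would then be lost.
3. State in Sample Size the visit from which the 10- and 17-point falls are counted, and report 1-year falls from the same visit.
4. Report by arm the share already <130/80 at week 2.

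The cost is wording, settled before the data are analysed; the readings should already be collected in both arms. The one visible downside is that within-arm falls counted from week 2 will look smaller. No change to the run-in, eligibility or treatment rules is proposed.

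### Constant-length randomization blocks within sex can be worked out from past allocations, so withholding the block size from allocating staff is weak protection; varying the length is a cheap, minor improvement

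*Protocol article*

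**What the plan says.** The randomization method is in the Procedures section of the protocol article.

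- Scheme: "Randomization is stratified by sex in blocks of equal size". Sex is the only stratification factor named, so there are two strata. The block length is not given.
- Second constraint: "we created 6 different permutations of the baseline survey, each with a different order of instruments, which are also balanced within blocks".
- Safeguard: "The research assistants responsible for arm allocation are blinded to block size to prevent contamination".
- Timing: "In week 2, participants undergo medication titration, the process of adjusting antihypertensive medication dosages to ensure appropriate and optimal treatment, and are then randomized".
- What follows allocation: "all study materials, including any equipment and/or materials, are distributed to the participants according to the treatment arm". The Medication Reminders section adds that staff help participants set up the app's reminders at randomization, and Table 1 shows that only one arm has the app and the activity tracker.
- Place: Clinical Setting puts every visit after enrolment in the emergency department at one research clinic.

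The article mentions no variation in block length and no masking of participants or clinic staff.

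**The concern.** With a constant length, each sex stratum returns to exact balance after every block. Anyone who sees the arms as they are allocated can look for the interval at which this happens. Not telling staff the number therefore hides something that past allocations reveal. Once the length is known, the last allocations in a block are often forced, and the others can be guessed better than by chance from the tally so far.

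What is at stake is selection before allocation. A person who expects a given arm might, without intent, influence which participant is randomized next or how a participant is handled just before randomization. Prognosis could then differ between arms for reasons other than chance.

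The stated reason for the safeguard is also misplaced. Contamination means that control participants are exposed to the intervention, and hiding the block size does nothing about that. What it can affect is whether the next allocation can be predicted.

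**Working it through.** **Plan's own figures.** The article gives no figure for predictability. The only number taken from it is the planned total of 396 randomized (198 per arm, Abstract and Sample Size). That base is sound: 30% against 47.5% at two-sided 5% and 90% power gives 161 per arm, and 161/0.81 = 198.8, which agrees with 198 to within one participant.

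**Block length.** Six survey orders balanced within a block require a multiple of 6, or of 12 if each order is also balanced by arm. Lengths 6 and 12 are therefore worked through. Both are assumptions, since the article states no length.

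**Allocations that are certain once the length is known.** In a 1:1 permuted block of length B = 2b, the expected number of forced allocations is 2b/(b+1), so their share is 1/(b+1).

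- B = 6 (b = 3): 1/4 = 25.0%; 396 × 0.250 = 99.
- B = 12 (b = 6): 1/7 = 14.3%; 396/7 = 56.6, about 57.

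**Correct guesses when the arm that is behind is always chosen.** The share is [b + (4^b / C(2b,b) − 1)/2] / B, against 50% by chance.

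- B = 6: [3 + (64/20 − 1)/2]/6 = 4.10/6 = 68.3%.
- B = 12: [6 + (4096/924 − 1)/2]/12 = 7.716/12 = 64.3%.

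**How soon the length shows itself.** This was simulated with 198 participants per sex (an even split, assumed) and an observer who sees the stratum from its start. All shorter candidate lengths are ruled out after a median of 8 allocations at B = 6 (90th percentile 28) and 20 at B = 12 (90th percentile 50). Longer multiples of the true length stay formally possible, so the observer is taking the shortest length that fits.

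**With lengths 6, 12 and 18 drawn at random with equal probability.** Suppose, unfavourably to the change, that the observer knows where each block starts but not its length. An allocation is certain only when one arm has reached 9, which happens only in a block of 18.

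- Forced allocations in a block of 18: 2 × 9/10 = 1.8.
- Mean block length: (6 + 12 + 18)/3 = 12.
- Share certain: (1.8/3)/12 = 5.0%; 396 × 0.05 = about 20.

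An observer who knows the set of lengths but must also infer where blocks start does worse: about 2% certain in simulation.

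For tally guessing, a block of 18 gives [9 + (262144/48620 − 1)/2] = 11.196 correct guesses. The average over the three lengths is (4.10 + 7.716 + 11.196)/3 = 7.67 per 12 allocations, or 63.9%.

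| Scheme | Certain | Tally guess correct |
|---|---|---|
| Constant 6 | 25.0% (99) | 68.3% |
| Constant 12 | 14.3% (57) | 64.3% |
| Random 6/12/18 | 5.0% (20) | 63.9% |

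**The case against.** The strongest reply is that little can be done with a good guess in this trial.

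- **Selection comes mostly before allocation can be foreseen.** Consent, the emergency department blood pressure criteria and the week-0 check all precede the week-2 randomization. To influence entry, staff would have to foresee a position in the sequence well ahead, within sex, without knowing who will attend.
- **Measurement and titration follow set procedures.** Clinic blood pressure is taken with an automated device, and titration follows an algorithm with a pill-count rule.
- **The analysis adjusts.** The models for both coprimary outcomes include baseline blood pressure and other patient characteristics, so steering on blood pressure itself would be partly corrected.
- **One clinic is not one team.** The article does not say that the allocating assistants also schedule or titrate.
- **The remedy is partial.** Tally guessing is about 64% after the change, hardly below constant blocks of 12.

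All of this stands and limits the point. It leaves the order and timing of week-2 visits, and handling just before randomization, as the main openings. It does not rescue the safeguard: a constant length can still be inferred, and making it vary still removes most of the certain allocations.

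The phrase about equal size could also mean that the same length is used for both sexes. The plain reading is a constant length. If lengths do vary, one sentence would settle the matter.

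**Conclusion.** The point holds as a minor weakness. As written, a constant length within two sex strata, protected only by not naming it, leaves about 14% (length 12) to 25% (length 6) of allocations certain in advance to someone who has tracked the sequence. This assumes that the length is 6 or 12 and that such a person sees the allocations in each sex in order.

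Two stronger readings are tempting, and the article does not support them.

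- **That the coprimary results would be biased by a calculable number of mmHg.** That needs an assumed difference in prognosis between participants whom staff favour and those whom they do not, and assumes that staff act on every guess. The article supports neither, and such a sum would also ignore the adjustment for baseline blood pressure. The size of any bias cannot be estimated from it.
- **That allocation is not concealed.** How each arm is released is detail that an article may leave to the full protocol, so its absence shows nothing. Concealing the next entry and preventing its prediction are separate matters, and only the second is at issue here.

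Lengths that are not multiples of 6, such as 4, should not be used to illustrate the problem, because they do not fit the survey-order balance.

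**What to change.** For allocations still to be made:

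1. Replace blocks of equal size with permuted blocks whose length varies at random within sex, in multiples of 6 so that survey-order balance is kept (for example 6, 12 and 18). Start at the next block boundary in each stratum. If survey order is also balanced by arm, use multiples of 12 instead. Lengths 12 and 24, equally likely, give a similar result: a block of 24 has 24/13 = 1.846 forced allocations, and (1.846/2)/18 = 5.1% certain.
2. Reveal each participant's arm only after the week-2 pre-randomization steps have been recorded. This matters because varying the length barely changes tally guessing. It concerns the order of recording only, not the content of any treatment decision.
3. State the purpose of masking block size as preventing prediction of the next allocation, not preventing contamination.

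The cost is a regenerated list and a short amendment, with no extra participants or visits. The downside is a possible imbalance of a few participants per stratum if the last block is incomplete.
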